### Statistical methods

Statistical analysis will follow the modified intention-to-treat principle [14]. Analysing the primary outcome, logistic regression of PEWS on unplanned PICU admissions will be performed to determine odds ratios (ORs) and 95% confidence intervals (CIs). The analysis will be adjusted for age. In the secondary outcome analysis, categorical data will be analysed using the chi-square test. Continuous data that are not normally distributed will be analysed using the Mann-Whitney *U* test. A *p* value <0.05 is considered significant.The two PEWS tools will also be evaluated using sensitivity, specificity and the receiver operating characteristic curve. In this study, sensitivity is the ability of the PEWS tool to correctly identify children at risk of an unplanned transfer to the PICU. Specificity is the ability of the tool to demonstrate a low score among children who are not at risk of an unplanned transfer to the PICU; thus, a low specificity indicates a high rate of false positives. Sensitivity and specificity will be calculated to measure the validity of the tools and the most predictive score for an unplanned transfer to the PICU. As the PEWS must be able to identify children at risk of acute life-threatening conditions and provide a ‘window’ for intervention, data analysis will stop one hour prior to the occurrence of the acute life-threatening condition to avoid overestimating the effect of the PEWS.

Descriptive statistics will be calculated to describe baseline variables and clinical characteristics. The descriptive analysis will be summarised as percentages, with median and interquartile ranges provided for continuous variables. STATA version 10 will be used for the analyses.

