**Methods/design:**

This is a multicentre, randomised, controlled clinical trial where children are allocated to one of two different PEWS models. The study involves all paediatric departments and one emergency department in the Central Denmark Region. The primary outcome is unplanned transfer to the paediatric intensive care unit or transfer from regional hospitals to the university hospital. Based on preliminary data, 14,000 children should be included to gain a power of 80% (with a 5% significance level) and to detect a clinically significant difference of 30% of unplanned transfers to intensive care or from regional hospitals to the paediatric department at the university department. A safety interim analysis will be performed after inclusion of 7000 patients.

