### Outcomes

The primary outcome is the sum of unplanned transfers to the PICU and transfers from regional hospitals to the university hospital or the number of deaths. Transfers from regional hospitals to the paediatric department at the university hospital are equated with transfers to the PICU; children who need intensive care at the regional hospitals will be transferred to the paediatric department at the university hospital to ensure proximity to the PICU.

The secondary outcomes are as follows:Paediatric Index of Mortality scoreSeverity of illness during PICU stay based on invasive ventilation and inotropesLength of hospital stayLength of PICU stay

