### Sample size

A power calculation was made based on accessible data from 2013 from the departments that are currently employing PEWS models. The available preliminary data showed 154 unplanned transfers to the PICU out of 10,000 admissions. With a power of 80%, a 5% significance level and an expected 30% reduction in the number of transfers to intensive care, we would have to include 7112 children in each group. The total available study population is 26,800 children annually.

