**Fig. 2 Fig2:**
[figure not shown]
SPIRIT study schedule

Separate interactive registration modules in the electronic patient chart were designed for each of the two PEWS models. The study data are extracted from the electronic patient charts. Thus, healthcare professionals in each department are responsible for data collection and data entry into the electronic patient chart as well as for obtaining consent from the parents.

For each patient included in the study, the following data are collected:Baseline demographics: child’s age, gender, pre-existing conditions, diagnostic category (cardiac, post-surgical, neurological, respiratory, infection, hydration)Clinical characteristics: discharge diagnosis, triage level at admission, time of day of critical event (day, evening, night)PEWS parameters and temperature in the 24 hours preceding transfer to the PICU, ending one hour before transfer to the PICUFrequency of PEWS and temperature measurements during the last 24 hours prior to transfer to the PICU, ending one hour before transfer to the PICUData from PICU: PIM3 scoreOutcome data: unplanned transfer to the PICU or university hospital, length of hospital stay, length of PICU stay

Transfers to the PICU and transfers from regional hospitals to the university hospital will be identified from the electronic patient charts. Two researchers will review each of these medical records to exclude planned transfers. These are transfers that are elective or planned in advance, transfers coming directly from the operating room and transfers in which the need for PICU care was due to the need to recover from sedation.

This trial will follow the recommendations from the Consolidated Standards of Reporting Trials (CONSORT) statement for non-pharmacological treatment interventions.

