### Data monitoring

A Data and Safety Monitoring Committee (DSMC) will perform a safety interim analysis when 7000 of the 14,000 patients have been randomised. In the safety analysis, the two PEWS models will be compared in terms of transfers to the PICU or transfers from regional hospitals to the university hospital. An independent statistician will perform the analysis and provide the results to the DSMC. To give recommendations on whether the trial should terminate or continue, the DSMC will use the Haybittle-Peto statistical approach as a guide [15]. The final decision regarding termination or continuation of the trial will be made by the research group, which consists of the principal investigator and three other members. Depending on the recommendations of the DSMC, further safety analyses could be performed. The safety analysis has been performed, and the DSMC had no comments.

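### The primary logistic regression is specified on unplanned PICU admissions, which does not match the primary outcome: deaths are left out on any reading, and regional-to-university transfers are left unclear

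*Protocol article*

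**What the plan says.** All references are to the protocol article.

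- **Outcomes.** The primary outcome is defined here as the "sum of unplanned transfers to the PICU and transfers from regional hospitals to the university hospital or the number of deaths". The next sentence adds: "Transfers from regional hospitals to the paediatric department at the university hospital are equated with transfers to the PICU".
- **Abstract, Methods/design.** "The primary outcome is unplanned transfer to the paediatric intensive care unit or transfer from regional hospitals to the university hospital". Death is not mentioned.
- **Statistical methods.** "Analysing the primary outcome, logistic regression of PEWS on unplanned PICU admissions will be performed", with adjustment for age. No other dependent variable is given for the primary outcome.
- **Data collection and management.** The outcome data are listed as "unplanned transfer to the PICU or university hospital, length of hospital stay, length of PICU stay".
- **Data monitoring.** At the safety interim, "the two PEWS models will be compared in terms of transfers to the PICU or transfers from regional hospitals to the university hospital".
- **Sample size.** "The available preliminary data showed 154 unplanned transfers to the PICU out of 10,000 admissions". The 30% reduction is stated there for transfers to intensive care; the abstract states the same 30% for both kinds of transfer.

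**The concern.** A primary analysis should have the primary outcome as its dependent variable. Here the outcome has up to three components and the model names one.

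Two consequences follow. First, a child who dies on the ward without a prior transfer stays in the denominator and is coded as a non-event, so such a death favours the arm in which it happens. Second, if the sentence is followed literally, a child moved from a regional hospital because of deterioration, but never admitted to the PICU, is also a non-event, although the hypothesis concerns exactly such children.

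The definition also matters for the credibility of the result. The section on sequence generation says that patients, clinicians and the research team are not blinded. If the wording supports more than one endpoint, the choice between them can be made, or can appear to have been made, after results by arm are visible. A later analysis plan could add detail, but the article itself states both the outcome and the model, and they differ.

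**Working it through.** **Step 1. Components named in each place**

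| Section | Unplanned PICU transfer | Regional-to-university transfer | Death |
|---|---|---|---|
| Outcomes | yes | yes | yes |
| Abstract | yes | yes | no |
| Statistical methods (primary model) | yes | not named | no |
| Data collection (outcome list) | yes | yes | not listed |
| Data monitoring (interim) | yes | yes | no |
| Sample size (planning rate) | yes | not named | no |

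The Outcomes section equates regional transfers with PICU transfers. Applied to the primary model, that could fill the second column. Nothing in the article equates death with PICU admission, so the third column stays empty for the model. A child who dies after an unplanned transfer is still an event through the transfer; only deaths without one are miscoded.

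**Step 2. The plan's own figure**

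Inputs (Sample size): control rate p1 = 154/10,000 = 0.0154; p2 = 0.7 × 0.0154 = 0.01078; 80% power; 5% significance, taken as two-sided. Allocation is 1:1.

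With d = p1 − p2, p̄ = (p1 + p2)/2, s0 = √[2p̄(1 − p̄)] and s1 = √[p1(1 − p1) + p2(1 − p2)]:

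n per arm = [(1.960·s0 + 0.842·s1)/d]²

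Here d = 0.00462, p̄ = 0.01309, s0 = 0.1607 and s1 = 0.1607, giving n = 9500 per arm. The stated 7112 is not reproduced. That is a separate matter; nothing below uses 7112.

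**Step 3. What the definition could do to power**

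Power = Φ[(d·√n − 1.960·s0)/s1], with n = 14,000/2 = 7000 per arm.

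At 1.54%: d·√n = 0.00462 × 83.67 = 0.3865; 1.960 × 0.1607 = 0.3150; (0.3865 − 0.3150)/0.1607 = 0.445; Φ(0.445) = 0.672.

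The article does not say how the 154 events divide, so the ranges below are assumptions, each with a 30% reduction.

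*(a) 1.54% is already the composite, and the model uses PICU admissions only*

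| PICU share of composite | Control rate | Power |
|---|---|---|
| 100% | 1.54% | 67% |
| 75% | 1.155% | 55% |
| 50% | 0.77% | 40% |
| 25% | 0.385% | 22% |

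*(b) 1.54% is PICU-only (67% power), and the composite is more frequent*

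| Composite relative to PICU-only | Control rate | Power of the composite |
|---|---|---|
| 1.25 times | 1.925% | 77% |
| 1.5 times | 2.31% | 84% |
| 2 times | 3.08% | 93% |

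*(c) Deaths alone.* With an assumed 0.02% to 0.1% of children dying without transfer, added to 1.54%: if the death rate is the same in both arms, power goes from 67.2% to between 66.5% and 64.0%; if deaths also fall by 30%, it goes to between 67.7% and 69.9%. Either way the shift is about 3 percentage points at most.

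**The case against.** The strongest defence is the equivalence sentence in Outcomes. The model sentence opens by saying that it analyses the primary outcome, so PICU admissions may simply be shorthand for both kinds of transfer. The Sample size section and the Discussion may use the same shorthand. This stands as far as it goes: a reader might infer that the regression certainly drops every regional transfer, and the article does not support that. Nor does it remove the ambiguity, because the abstract, the data list and the interim comparison name both kinds separately. It also does nothing for deaths.

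Three other inferences go too far:

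- *That three rival primary outcomes are in force.* Only the abstract and Outcomes define a primary outcome, and they differ on death. The data list and the safety comparison are not definitions, and Statistical methods names a model variable.
- *That the mismatch costs a known amount of power, say from 79% to 67%.* This needs a composite rate of 2.05%, obtained by solving backwards from 7112. That sample size does not follow from the stated inputs, and no section gives such a rate.
- *That death is not being collected.* The list in the article is condensed; it also leaves out invasive ventilation and inotropes, which belong to a stated secondary outcome. Absence from it does not show that the field is not extracted.

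It is also fair to say that deaths are likely to be few. The Discussion describes in-hospital arrest or death as having a low event rate in this age group.

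**Conclusion.** The point holds: the stated primary analysis does not match the stated primary outcome. It is firm for deaths, which Outcomes includes and which the model excludes on any reading. For regional transfers the text is ambiguous, not a definite exclusion.

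The size cannot be fixed from the article. Leaving out deaths alone probably matters little for power, but each death without transfer is counted in the wrong direction. Leaving out regional transfers could matter a great deal: from no loss, if nearly all events are PICU admissions, to the low powers in table (a) or the forgone gain in table (b). Those figures rest on an assumed split, a common 30% reduction in every component, a two-sided 5% test without age adjustment, and 7000 per arm. The conclusion does not depend on them.

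**What to change.** Before the final analysis, define one outcome per randomised child, yes or no: unplanned PICU transfer, unplanned regional-to-university transfer for deterioration, or death, as in Outcomes. Then:

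- Put this composite in place of unplanned PICU admissions as the dependent variable of the logistic regression. A per-child definition also resolves the difference between a sum of events in Outcomes and a binary model in Statistical methods.
- Use the same definition in the abstract, Outcomes, Sample size, Data collection and Statistical methods, and say in Sample size which components the 154 events cover.
- Make sure that death is extracted from the electronic chart and is included in any further safety comparison.

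The cost is changes of wording and, if it is not already extracted, one more field from the chart. No change to recruitment or conduct is needed.

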## Methods/design

### Study setting

The study is ongoing in four paediatric departments, four paediatric emergency and assessment units, one emergency department and a specialised paediatric unit for children with neurological illness in the Central Denmark Region. Including both a university hospital and several regional hospitals helps ensure the highest possible diversity in the population and strengthens the study’s generalisability. The participating departments are listed on the project homepage (www.pews.dk). None of the participating hospitals had been working with any kind of PEWS model prior to this study.

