### Allocation

The departments will all have access to a web-based randomisation programme, Trialpartner. Each patient receives his or her own randomised number. If a patient is readmitted during the inclusion period, observation will continue based on the result of the initial randomisation. Consecutive eligible patients are randomly allocated with a 1:1 ratio to one of the two PEWS tools. There is no stratification at the patient or institution level.

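### The primary model adjusts for age only; adding hospital and pre-existing conditions would be a free but small improvement to an analysis that is already valid

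*Protocol article*

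**What the plan says.** Statistical methods in the protocol article fixes a logistic regression for the primary outcome, giving an odds ratio with a 95% confidence interval, and adds: "The analysis will be adjusted for age". No other covariate is named, and no reason is given for choosing age alone.

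Allocation describes simple 1:1 randomisation through a web programme: "There is no stratification at the patient or institution level".

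Study setting stresses the mix of sites: "Including both a university hospital and several regional hospitals helps ensure the highest possible diversity in the population". Outcomes then makes one event component depend on where the child is: "Transfers from regional hospitals to the paediatric department at the university hospital are equated with transfers to the PICU".

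Data collection and management lists pre-existing conditions under baseline demographics. Under clinical characteristics it lists "discharge diagnosis, triage level at admission, time of day of critical event". Hospital is not in the list. It must still be known, because departments enrol the children themselves and inter-hospital transfers are identified from the charts.

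**The concern.** Neither the randomisation nor the primary model takes account of hospital. A child at a regional hospital can reach the endpoint through transfer to the university hospital; a child already there can reach it only through unplanned PICU transfer or death. It is therefore plausible that event rates differ between sites. Pre-existing conditions are plausibly prognostic too.

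A primary model that omits prognostic baseline factors can lose some power and keeps whatever chance imbalance arises in them. If an imbalance appears and covariates are added afterwards, the choice is data-driven, in a trial where clinicians and the research team are unblinded. The stake is thus a little power and protection against a later argument over covariates. The validity of the comparison is not in question.

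**Working it through.** **Inputs from the documents.** Control event rate 154/10,000 = 1.54%; 30% reduction, giving 0.7 × 1.54% = 1.078%; 80% power; 5% level (taken as two-sided); 7112 per group stated; 14,000 in total, so 7000 per arm (Sample size; Abstract). The dependent variable is taken to be the event as defined in Outcomes.

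**Assumed, because the documents give no figure.** Half the children at regional hospitals; four triage levels with shares 5/20/40/35%; odds ratios of 1.5 to 4 for hospital type and 1.5 to 5 per triage step.

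**Step 1: the plan's own figure.** With n = [1.96 √(2p̄(1−p̄)) + 0.8416 √(p₁(1−p₁) + p₂(1−p₂))]² / (p₁−p₂)² and p̄ = 1.309%, the numerator is (0.3150 + 0.1353)² = 0.2028 and the denominator is 0.00462² = 0.00002134. This gives 9500 per group, not 7112. With 7000 per arm the power is 67.2%. That shortfall is a separate matter; 67% is simply the baseline here.

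**Step 2: what sets the standard error.** Expected events are 7000 × 0.0154 + 7000 × 0.01078 = 108 + 75 = 183. The standard error of the log odds ratio is about √[1/(7000 × 0.0154 × 0.9846) + 1/(7000 × 0.01078 × 0.98922)] = √(0.00942 + 0.01340) = 0.151. With so few events, the event count fixes it almost entirely.

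**Step 3: effect of adjustment.** 14,000 children were simulated, with 10,000 runs per scenario, comparing arm alone with arm + hospital type + triage. Age is in neither model, because no age effect is given. Hospital type and triage stand in for whichever baseline covariates are used.

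| Assumed OR, hospital type / per triage step | AUC | SE of log OR, without → with | Mean OR, without → with | Power, without → with |
|---|---|---|---|---|
| 1.5 / 1.5 | 0.61 | 0.1518 → 0.1520 | 0.695 → 0.695 | 67.6% → 67.4% |
| 2 / 2 | 0.69 | 0.1518 → 0.1525 | 0.696 → 0.693 | 67.2% → 67.8% |
| 3 / 3 | 0.78 | 0.1519 → 0.1539 | 0.695 → 0.688 | 66.7% → 67.7% |
| 4 / 5 | 0.87 | 0.1519 → 0.1569 | 0.695 → 0.678 | 66.8% → 69.8% |

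The changes are −0.2, +0.6, +1.0 and +3.0 points. Under no treatment effect, both models rejected in 4.8% to 5.1% of runs in every scenario.

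**Step 4: where the gain comes from.** In the last row, ln(0.695)/0.1519 = −2.40 without adjustment and ln(0.678)/0.1569 = −2.48 with it. The standard error rises. The test gains only because the conditional odds ratio moves further from 1.

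**Step 5: chance imbalance.** The SD of the between-arm difference in a covariate share is at most √(0.5 × 0.5 × 2/7000) = 0.85 percentage points. If half the children are regional and carry three times the risk, mean risk is proportional to 1 + 2s, where s is the regional share. The log risk then changes by 2/(1 + 2 × 0.5) = 1 per unit of s. A 1-SD imbalance therefore shifts the log odds ratio by about 0.0085, or 0.0085/0.152 = about 6% of one standard error.

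**The case against.** The strongest reply is that nothing here is wrong. One model with one baseline covariate is fixed in advance, and that is a valid analysis of a 1:1 randomised trial. This stands.

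Three stronger readings are tempting, and the documents support none of them.

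- **That unstratified randomisation obliges adjustment for hospital.** The usual obligation runs the other way: factors used to stratify belong in the model, and here there were none.
- **That the age-only model wastes precision on a material scale.** A reader might approximate explained variance as R² = CV² × p/(1−p), where CV is the coefficient of variation of the children's baseline risks, and divide the sample size by 1 − R². With CV assumed to be 1.5 to 3 and p = 1.31%, R² is 3% to 12% and power appears to rise to 68–73%. That treats a logistic model as a linear adjustment and credits all of R² to the new covariates although age is already in the model. It also assumes very strong predictors: CV is only about 0.8 for odds ratios of 2, 1.4 for 3, and 2.2 even in the extreme scenario. Model standard errors rise rather than fall.
- **That hospital and triage are known to predict the event strongly.** The documents give no event rate by site and no association with triage. Plausible is as far as they go.

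Triage needs a further caution. It is listed beside discharge diagnosis, its timing relative to allocation is not stated, and staff are unblinded. Entering it unchecked could mean adjusting for something measured after randomisation.

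What remains is that hospital and pre-existing conditions are baseline, available and plausibly prognostic, and that using them needs no new data.

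**Conclusion.** This is a low-severity, free improvement. The age-only comparison keeps its type I error and can be reported as planned without misleading anyone.

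Pre-specifying hospital and pre-existing conditions would bring about 0 to 1 point of power for covariate odds ratios up to 3, and about 3 points at most in an extreme case. It would also remove a small chance shift and forestall a later choice of covariates. These sizes rest on assumed prognostic strengths, an assumed half of children at regional hospitals, and a simulation without age. Because age is already in the planned model, any overlap with it would reduce the gain.

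The change does not repair the sample size: even the extreme case reaches only 69.8% power, against the 80% the plan claims.

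**What to change.** Before analysis, and before any comparison of outcomes by arm informs the choice, pre-specify the primary logistic model as arm + age + hospital + pre-existing condition. Take hospital as the one where the child was randomised, and use hospital type instead if some sites have too few events for their own term.

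Add "triage level at admission" only if it is confirmed to be recorded before allocation. Do not adjust for discharge diagnosis or time of the critical event, which arise after randomisation. Keep the age-only model as a sensitivity analysis.

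The cost is one line in the analysis plan and no new data collection. The downside is that the adjusted odds ratio is conditional on more covariates and will differ slightly from the age-only one: in the simulated scenarios the mean moved from 0.695 to no lower than 0.678. The report should say which odds ratio is primary.
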